### Expected results

**
*Validation of VSCT outcomes*
**

We expect SCT mean accuracy to be positively correlated with performance on the CORSI backward task and VSCT accuracy.

A positive correlation with SCT accuracy would validate VSCT as a measure of participants' abilities to maintain and retrieve cognitive maps based on allocentric frameworks (
Burles *et al*., 2017). Both SCT and VSCT require creating an allocentric cognitive map from multiple egocentric viewpoints. Therefore, we expect a positive correlation between SCT mean accuracy and spatial working memory, as measured by the Corsi backward task. Regarding reliability, based on our planned analyses, we expect to find acceptable to high internal consistency for key performance metrics (e.g., accuracy, error scores), as assessed through split-half reliability and/or Cronbach’s alpha, depending on the distributional properties of the data. Additionally, we anticipate that test–retest reliability in a subsample will demonstrate moderate to high stability over time, supporting the robustness of both the SCT and VSCT as reliable tools for assessing spatial cognition.

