We will use a series of tests and tasks to validate the VSCT. We hypothesize a positive correlation between the VSCT and SCT, as both are designed to measure the same construct—namely, the ability to form cognitive maps. We also hypothesize a positive correlation between the VSCT and Backward Corsi, as working memory is a key component in the formation and maintenance of cognitive maps (
Epstein *et al.*, 2017). Conversely, we do not expect a significant correlation between the VSCT and RAVLT. We included the Rey Auditory Verbal Learning Test (RAVLT) in our study precisely to assess discriminant validity. The RAVLT measures verbal episodic memory, while the VSCT targets visuospatial configuration memory—two constructs that are theoretically and empirically distinct (
Suri *et al.*, 2017). By including the RAVLT and confirming that it does not significantly correlate with performance on the VSCT, we provide evidence that the VSCT is not simply capturing general memory ability, but rather a more specific visuospatial memory component. This lack of correlation supports the discriminant validity of our task, helping to confirm that it measures a construct different from that assessed by standard verbal memory tasks.

Finally, to evaluate VSCT feasibility we will use the Simulator Sickness Questionnaire (SSQ) (
Kennedy *et al*., 1993).

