### Participants

As the study aims to evaluate
**convergent and discriminant validity** of VSCT, by comparing VSCT correlation with SCT to the correlation of RAVLT with SCT, an
*a priori* power analysis was conducted using

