**G*Power 3.1**
Faul *et al.* (2009). Assuming a
**moderate to large effect size (Cohen’s q = 0.4)**, a significance level of
**α = 0.05**, and a desired power of
**0.95**, The required sample size for comparing two independent correlation coefficients using a z-test for dependent Pearson’s r was calculated as 166
**participants**. Taken this for granted, and bearing in mind that the data to correlate are not yielded with a paper-and-pencil questionnaire- but a virtual setting requiring training and adaptation, we weight the effect size indication with previous research using similar aims and methods.

This was the case in
da Costa *et al.* (2022), who validated two immersive virtual reality tasks for spatial orientation using correlational and group comparison analyses. The authors reported significant associations between the virtual tasks and traditional cognitive measures, as well as successful group discrimination.

The participants represented a sample size large enough to yield statistically reliable confidence intervals. It should be noted that the study employed a between-subjects design; however, participants from the two groups were combined. In contrast, our study will correlate the two groups with two different variables.

Furthermore,
*
He *et al.* (2022)
* employed a fully within-subjects design to validate a spatial perspective-taking task in ambulatory virtual reality, using a sample size comparable to ours. However, since within-subjects designs typically offer greater statistical power, we acknowledge that our between-subjects design may require a larger sample to achieve equivalent sensitivity. We have accounted for this by adopting a conservative effect size estimate and grounding our decision in the specific demands of VR-based testing, which introduces variability due to training and adaptation phases.

Participants will be actively recruited to participate in the intervention across various University of Bologna Campus locations. Recruitment will be facilitated through targeted advertisements and consecutive enrollment procedures to ensure diverse participant representation and data robustness. 

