### Correlation analysis

We will run correlations matrix between CORSI, SBSOD, and hits at both the VSCT and SCT. This will help us understand the influence of general intelligence and working memory capacity on spatial ability and ensure that the VSCT and SCT are comparable tasks

Regarding reliability, we plan to assess internal consistency using split-half and/or Cronbach’s alpha methods for key performance metrics (e.g., accuracy, error scores), depending on distributional characteristics. In addition, we aim to conduct a test–retest reliability study in a subsample of participants to examine stability over time.

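### The study is sized on a comparison of two correlations that the Plan of analysis never lists, while Expected results lets one positive correlation validate the task

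*Protocol article*

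**What the plan says.** All places are in the Protocol article.

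- **Methods, Participants.** The aim is convergent and discriminant validity, to be shown "by comparing VSCT correlation with SCT to the correlation of RAVLT with SCT". The sample size follows from that contrast, with q = 0.4, alpha 0.05 and power 0.95: "The required sample size for comparing two independent correlation coefficients using a z-test for dependent Pearson’s r was calculated as 166" participants. The same section adds that "our study will correlate the two groups with two different variables", so the two correlations come from different people.
- **Validation of a new 3D spatial task.** Three hypotheses are given: a positive VSCT-SCT correlation, a positive VSCT-Corsi correlation ("We also hypothesize a positive correlation between the VSCT and Backward Corsi, as working memory is a key component"), and no significant VSCT-RAVLT correlation, the last offered as the evidence of discriminant validity. Only the first SCT administration (T1) enters the correlations with the VSCT; T2 is exploratory.
- **Procedure.** Participants go to one of two groups. The VR group performs the VSCT and the AV group takes the RAVLT. Both take the SCT before and after.
- **Plan of analysis.** It lists t-tests between groups (SCT hits, Corsi, SBSOD), and then: "We will run correlations matrix between CORSI, SBSOD, and hits at both the VSCT and SCT". RAVLT is not in that matrix, and no test of a difference between correlations appears.
- **Expected results.** "A positive correlation with SCT accuracy would validate VSCT as a measure of participants' abilities to maintain and retrieve cognitive maps". This criterion has no discriminant element.

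**The concern.** The article states the test that decides validity in two ways that do not match. The sample size belongs to a difference between two correlations. The sentence that says what would validate the task asks only that one of those correlations be positive, and the Plan of analysis supplies only that one.

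The two criteria answer different questions. A positive r(VSCT,SCT) shows that the two spatial tasks share something, which may be general memory or general ability. The comparison with r(RAVLT,SCT) is what is meant to show that the shared part is spatial. If the plan is followed as printed, a report can claim validation with no discriminant evidence, although the article names discriminant validity as part of the aim. Much rests on that verdict: the article calls validity a necessary first step before longitudinal or interventional use, and its Discussion foresees therapeutic and educational use.

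**Working it through.** **1. Which criterion appears where**

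| Criterion | Participants (aim, sample size) | Introduction (hypotheses) | Plan of analysis | Expected results |
|---|---|---|---|---|
| r(VSCT,SCT) greater than r(RAVLT,SCT) | yes | no | no | no |
| r(VSCT,SCT) > 0 | no | yes | yes, matrix cell | yes, as the validating result |
| r(VSCT,RAVLT) not significant | no | yes | no | no |

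The third row cannot be computed from the design described: no participant is scheduled for both the VSCT and the RAVLT. The first row can be computed, because both groups take the SCT at T1. It is therefore the only discriminant test the design supports, and it is the one missing from the Plan of analysis.

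**2. The plan's own figure**

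For two independent correlations compared on the Fisher z scale:

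n per group = 2 × ((z for alpha + z for power) / q)² + 3

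Two-sided alpha 0.05, power 0.95, q = 0.4: 2 × ((1.960 + 1.645) / 0.4)² + 3 = 165.4, so 166 per group. The figure of 166 reproduces for the difference of correlations, which confirms that the study was sized on that contrast. It reproduces as a per-group number, whereas the text gives it as the number of participants. That is a separate matter, so both readings are carried below: 83 per group (166 in total, split 1:1) and 166 per group.

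**3. How often the two criteria part company**

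Inputs: two-sided 0.05 (the article does not state sidedness), 1:1 allocation (not stated), and assumed true correlations (the article gives only q).

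- Single correlation: mean of z = atanh(r1) × √(n − 3); success if z exceeds 1.96.
- Difference: mean of z = (atanh r1 − atanh r2) / √(2 / (n − 3)); success if z exceeds 1.96.
- The two statistics share r(VSCT,SCT), so they correlate 1/√2, about 0.71.

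Example, r1 = 0.38, r2 = 0, n = 83: atanh(0.38) = 0.400. The single correlation has mean z = 0.400 × √80 = 3.58, success 95%. The difference has mean z = 0.400 / √(2/80) = 2.53, success 72%. The single correlation succeeds and the difference fails in 24%.

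| Assumed r(VSCT,SCT) vs r(RAVLT,SCT) | q | n per group | Single succeeds | Difference succeeds | Single succeeds, difference fails |
|---|---|---|---|---|---|
| 0.38 vs 0 (design effect) | 0.40 | 83 | 95% | 72% | 24% |
| 0.38 vs 0 (design effect) | 0.40 | 166 | >99% | 95% | 5% |
| 0.40 vs 0.15 | 0.27 | 83 | 97% | 41% | 56% |
| 0.40 vs 0.15 | 0.27 | 166 | >99% | 69% | 31% |

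In these four cases the reverse (difference succeeds, single correlation fails) occurs in less than 1% of studies. The disagreement runs one way: the criterion in Expected results passes and the sized contrast does not.

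**The case against.** **A difference of correlations always has less power than a single one, and the two address different questions.** Convergent and discriminant evidence may disagree without contradiction, and part of the gap in the table is simply the difference in power. This stands, and it is why the percentages measure the consequence rather than prove the defect. The defect is that Expected results attaches validation to the convergent half alone, when the stated aim has both halves.

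**The size depends on the scenario.** This also stands. At the protocol's own q = 0.4, with 166 per group, the conflict is only 5%. The larger figures need a smaller true difference or 83 per group.

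**The article condenses a fuller plan.** Detail on testing may sit in a document not shown here. That would excuse silence, but the sizing contrast and the validating criterion are both printed, and they differ.

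**A tempting stronger reading** is that the plan runs many correlations at full alpha, so that some cell will support validity by chance. The article does not say this. Alpha 0.05 appears once, for the power calculation; no passage says that any one significant cell would count as validation; and test order or an alpha split may be set in an analysis plan not shown. One hypothesis, VSCT-RAVLT, is supported by non-significance, to which this kind of inflation does not apply. Nor is it quite fair to say that the article gives no lead on the main contrast: Participants ties the aim to the correlation difference. The fault is that the later sections do not follow it.

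**Conclusion.** The point holds as an internal contradiction about the deciding test. The aim and the sample size rest on r(VSCT,SCT) against r(RAVLT,SCT); the Plan of analysis omits that comparison; and Expected results declares validation on a positive VSCT-SCT correlation alone. The discriminant criterion given in the Introduction cannot be evaluated in the design described.

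The consequence ranges from 5% of studies (design effect, 166 per group) to 56% (0.40 vs 0.15, 83 per group) in which the task would be called validated while the sized contrast fails. These figures assume the true correlations shown, a two-sided 0.05 test and equal groups. The contradiction itself needs none of these assumptions. No claim about family-wise error is made. The change should be made before data are seen.

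**What to change.** 1. In the Plan of analysis, Correlation analysis, add the Fisher z comparison of r(VSCT, SCT at T1) in the VR group with r(RAVLT, SCT at T1) in the AV group.
2. In Expected results, state that the VSCT is considered validated only if r(VSCT, SCT at T1) is positive and significant and the comparison in item 1 also succeeds. A positive correlation alone is to be reported as convergent evidence only.
3. In the Introduction, replace the non-significant VSCT-RAVLT correlation as the discriminant criterion with the comparison in item 1, since no participant takes both tests.
4. Report the other matrix cells (Corsi, SBSOD) as supportive, with 95% confidence intervals.

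Because both criteria in item 2 must be met, no alpha split is needed. The cost is a change of wording in the article and in the OSF protocol. The change in itself adds no participants or measurements; whether 166 is a total or a per-group number has to be settled separately. The downside is that validation becomes harder to claim: at the design effect the chance of meeting both criteria is about 71% with 83 per group (95% − 24%) and about 95% with 166 per group, against 95% and over 99% for the single correlation.

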## Discussion

The proposed study protocol aims to validate a novel Virtual Spatial Configuration Task (VSCT), designed to evaluate participants' cognitive map formation abilities. This validation is crucial as it establishes the reliability of the VSCT in assessing spatial orientation skills. By requiring participants to explore a virtual environment, learn spatial relationships between landmarks, and recall their positions, the task offers a comprehensive measure of spatial cognition.

The development of the VSCT addresses a significant gap in spatial cognition research, particularly the lack of programs designed to assess higher-level spatial abilities, such as cognitive map formation, in 3D VR environments. Although some research groups have proposed VR-based spatial tests (e.g.,
Gehrke *et al*., 2018;
Hartman *et al*., 2006), to the authors' knowledge, no specific validations of VR assessment tasks in immersive virtual environments have been conducted. Therefore, we believe it is important to address this gap and explore the opportunities that VR offers in the domain of spatial cognition assessment.

One of the innovative aspects of the VSCT is its potential application for populations with impaired movement. The task is designed to allow users to explore the environment by rotating in a movable chair, eliminating the need for forward or backward movement, making it particularly suitable for individuals with limited mobility or dexterity. This design simplifies interaction, reduces the complexity of movement controls, and enhances accessibility. Additionally, by limiting navigation to rotational exploration, the task minimizes the sensory mismatch that often leads to motion sickness, thereby improving user comfort and engagement. The VSCT's design strategically controls the visibility of virtual objects, requiring users to piece together information gradually. This approach encourages cognitive engagement and problem-solving as users integrate sequential observations to gain a comprehensive understanding of the environment. Such cognitive engagement is particularly beneficial for populations with impaired movement, as it provides a means to enhance spatial orientation and navigation skills without the need for physical locomotion. For instance, stroke survivors often experience limited mobility and spatial disorientation. The VSCT’s rotation-based exploration allows them to safely practice navigating a virtual environment. By gradually revealing objects as they turn, users strengthen spatial awareness and problem-solving skills without the need for walking or complex controls.

The task's reliance on proprioceptive feedback and vestibular system inputs significantly enhances its effectiveness in spatial learning and navigation. Unlike static 2D tasks, which fail to provide participants with sensory information from their own movements, this dynamic approach enables users to actively explore and interact with the environment. By integrating proprioceptive cues and vestibular inputs, participants receive continuous updates about their position and movements, allowing them to build and maintain accurate cognitive maps. This interactive, multi-sensory experience reflects the real-world processes of spatial encoding and navigation, underscoring the critical role of proprioceptive and vestibular feedback in enhancing the fidelity and robustness of spatial representations. In this context, it is also important to consider the applicability of this software for training spatial abilities after injury, which often involves some level of motor impairment. While previous studies have demonstrated the malleability of lower-level spatial functions, such as mental rotation and route memory, through various training interventions (
Montana *et al*., 2019;
Subrahmanyam & Greenfield, 1994;
Uttal *et al*., 2013), few have specifically targeted cognitive map formation. An exception is a study by
McLaren-Gradinaru and colleagues (2020), which evaluated the effects of training by comparing task performance before and after training. By providing an immersive virtual environment where participants can develop and refine their spatial orientation skills, the VSCT could serve the dual purpose of assessing and improving the ability to form cognitive maps.

The translational value of the VSCT extends beyond its immediate application in cognitive training and neurorehabilitation. By providing a validated tool for assessing and improving spatial orientation skills, the VSCT has the potential to be integrated into a wide range of therapeutic and educational programs. For individuals with neurodegenerative diseases, brain injuries, or developmental disorders, the VSCT offers a novel and engaging way to enhance spatial cognition and independence. Its use in virtual reality settings also opens up possibilities for remote and home-based interventions, making it a versatile tool for widespread application.

Beyond clinical populations, the VSCT could also hold significant value for broader groups at risk of spatial difficulties. For example, healthy older adults often experience age-related declines in spatial orientation that increase the risk of disorientation and falls; the VSCT may provide an engaging and safe way to monitor and train these abilities proactively. Similarly, in educational contexts, spatial ability is closely linked to achievement in STEM disciplines. Incorporating the VSCT into training curricula could provide students with opportunities to strengthen cognitive map formation skills that underlie problem-solving in fields such as mathematics, engineering, and the natural sciences. By extending its scope to these populations, the VSCT not only serves as a rehabilitative and diagnostic tool but also as a platform with the potential to foster resilience, independence, and academic success.

Looking to the future, the VSCT could be further refined and expanded to include more complex virtual environments and tasks. Integrating advanced features such as adaptive difficulty levels, real-time feedback, and multi-sensory integration could enhance its effectiveness and user experience. Additionally, research could explore the long-term effects of regular VSCT training on spatial cognition and daily navigation skills, providing valuable insights into its therapeutic potential. Future work could also compare chair-based and ambulatory VR setups to further assess the generalizability of findings across different navigation modalities.

## Conclusion

In conclusion, the validation of the VSCT represents a significant advancement in spatial cognition research. By providing an accessible, engaging, and effective tool for assessing and training spatial orientation skills, the VSCT holds promise for improving the quality of life for individuals with impaired movement and other cognitive challenges. Its translational value lies in its potential to be integrated into diverse therapeutic and educational programs, paving the way for innovative interventions and future research in the field.

## Declarations

### Ethics approval

The study was approved by the Bioethics Committee of the University of Bologna (approval number: n 0022813, dated 2024.01.06) and complies with the ethical standards outlined in the Declaration of Helsinki (1964).

### Consent to participate

Written informed consent will be obtained from all participants involved in this study. Ethical approval has already been granted by the Bioethics Committee of the University of Bologna under Protocol No. [0022813].

Participants will be provided with a detailed consent form outlining the study's objectives, procedures, potential risks, and their rights, including the right to withdraw at any time without consequences.

Furthermore, the full text of the informed consent document will be made available in the Extended Data to ensure transparency and adherence to ethical guidelines.

### Consent for publication

Not applicable, as this is a study protocol and does not include individual data or identifiable information.

## Data Availability

No data associated with this article. The data from the future experiment will be made available in accordance with open science principles. The research protocol has been drafted in the OSF repository with the following DOI:
https://doi.org/10.17605/OSF.IO/3DMSY (
[name] *et al*., 2024). All the materials, including study questionnaires, informed consent and supplementary data, are also published at this DOI. **
*Code availability*
** At the end of the project, the project source code will be published in a dedicated public repository on Git Hub to encourage further development and research (
https://github.com/[name]/VSCT). Data are available under the terms of the Creative Commons Attribution 4.0 International license (CC-BY 4.0) (
https://creativecommons.org/licenses/by/4.0/).
